### Outcomes

#### Primary outcome measure

The primary outcome is the change in the Tinnitus Functional Index (TFI) questionnaire from baseline to follow-up at three months. The TFI is a self-reported questionnaire assessing the impact of tinnitus on quality of life [31, 32]. The patient must answer 25 questions on a Likert scale in the range of 0–10. For questions 1 and 3, which are expressed in percentages, the Likert scale is transformed to a 0–10 scale post hoc. The total score is then calculated as the mean of all questions multiplied by 10 and expressed as a number between 0 and 100. Results of the TFI include the total score and the score on eight subscales: intrusiveness; sense of control; cognition; sleep disturbance; auditory difficulties; relaxation; quality of life; and emotional distress. A decrease of 13 points on the total TFI score is considered as a clinically relevant difference [32]. Based on previous studies, we expect mean TFI scores at baseline of approximately 50 [28].

#### Secondary outcome measures

Tinnitus Questionnaire (TQ)

The Dutch validated version of the TQ is used to differentiate between emotional and cognitive distress, auditory difficulties, and self-experienced intrusiveness caused by tinnitus [33]. The total score can be in the range of 0–84, assigning a subject to a distress category: slight (score = 0–30, grade 1); moderate (score = 31–46, grade 2); severe (score = 47–59, grade 3); and very severe (score = 60–84, grade 4) [34].Speech, Spatial and Qualities of Hearing Scale-12 questionnaire (SSQ12)

The SSQ12 is a short form of the Speech, Spatial and Qualities of Hearing scale [35, 36]. The questionnaire is used in clinical research to measure several aspects of hearing ability, such as: speech comprehension in quiet and noise; localization of sound, distance, and movement; segregation; and listening effort. Responders rate their ability to do or experience the situation described in each question by marking a 1–10 scale (1 = not at all, 10 = perfectly). Scores of all 12 questions are averaged to obtain a global SSQ-12 score.Hospital Anxiety and Depression Scale (HADS)

The HADS is used to detect states of anxiety or depression [37]. Patients must answer a total of 14 questions, of which seven belong to the subscale “depression” and seven pertain to the subscale “anxiety.” Scores of 7 or less on each subscale indicate non-cases. Scores of 8–10 are borderline abnormal (borderline case), while scores of 11–21 are abnormal (case).Visual Analogue Scale (VAS)

The VAS enquires the mean loudness and maximum loudness of the tinnitus. The patient must score their tinnitus loudness on a scale of 0 (absence of tinnitus) to 100 (cannot be any louder).Hyperacusis Questionnaire (HQ)

The patient’s hypersensitivity to sound is investigated using the 14-item HQ [38]. The 14 questions assess three dimensions (attentional, social, and emotional). The answer categories are: “no” (score of 0 points); “yes, a little” (1 point); “yes, quite a lot” (2 points); and “yes, a lot” (3 points). A total score of 28 or more indicates clinically significant hyperacusis.Health Utilities Index (HUI23)

The HUI23 is a family of generic health profiles and preference-based systems for the purposes of measuring health status, reporting health-related quality of life (QoL), and producing utility scores [39]. The HUI23 comprises a 15-item questionnaire. The resulting total health-related QoL score ranges from 0.00 (dead) to 1.00 (perfect health).Pure-tone audiometry

Pure-tone linear audiometry will be performed according to current clinical standards (International Organization for Standardization [ISO] 8253–1:2010), using a two-channel AC-40 audiometer (Interacoustics, Assens, Denmark) in a soundproof booth. Air conduction thresholds will be measured at 125 Hz, 250 Hz, 500 Hz, 1 kHz, 2 kHz, 3 kHz, 4 kHz, 6 kHz, and 8 kHz using headphones. When air conduction thresholds between 250 Hz and 4 kHz exceed normality levels of 20 dB HL, the bone conduction threshold will be measured at 250 Hz, 500 Hz, 1 kHz, 2 kHz, 3 kHz, and 4 kHz in order to distinguish between conductive and sensorineural hearing loss.Tinnitus analysis

Participants are asked whether they perceive the tinnitus unilaterally, bilaterally, or centrally, and whether the tinnitus sound is a pure tone, a noise, or a mixture of different sounds (polyphonic). Psychoacoustic characteristics of the tinnitus sound are assessed in a soundproof booth. As a psychoacoustic equivalent of frequency, the tinnitus pitch is obtained by use of a pitch matching technique. A two-alternative forced choice procedure will be employed using the contralateral ear as the reference ear. In cases where tinnitus is perceived bilaterally, the choice of ear is made arbitrarily. Using this technique, an attempt is made to identify the center pitch of the tinnitus. When multiple tinnitus sounds are perceived, patients are asked to focus on the most troublesome tinnitus sound. Pairs of pure tones (or noises in case of noise-like tinnitus), differing by one or more octaves, are presented to the individual, who has to indicate which of the stimuli best resembles the tinnitus sound. This procedure is repeated and finer adjustments are made to obtain the closest possible match of the tinnitus pitch.

Loudness is the perceptual correlate of sound intensity. The tone or noise defined as the pitch match is presented to the ipsilateral ear (when appropriate) and a loudness match is made by use of an alternating procedure. Because of compressed dynamic range frequently present at the tinnitus frequency, final loudness measurements are made with 1-dB steps. The absolute level of tinnitus loudness is measured in dB hearing level (dB HL). In addition, a calculation is made to provide a measurement of relative loudness expressed in dB sensation level (dB SL), which is defined as the level of the loudness match minus the auditory threshold at the tinnitus frequency.Changes in SPIQ and SPIN understanding

Speech comprehension in quiet is investigated using the Dutch NVA lists, which were developed by the Dutch Society for Audiology (Nederlandse Vereniging voor Audiologie, NVA) [40]. Each of the four lists consists of 12 monosyllabic words (consonant-vowel-consonant), of which the first one is used for training. The percentage of correctly identified items determines the speech recognition score. The lists are presented through headphones.

The Leuven Intelligibility Sentences Test (LIST) is used to measure speech reception in noise [41]. The long-term average frequency spectrum of the speech signal matches the spectrum of the noise. The noise level is constant at 65 dB SPL, while the sound level of the speech signal is changed according to the individual’s response. Lists of 10 sentences are presented through headphones. If the individual correctly repeats the keywords of a sentence, the sound level of the next sentence is decreased by 2 dB SPL. In case of an incorrect response, the level is increased by 2 dB SPL. The levels of the last five sentences of the list and the imaginary 11th sentence are averaged to acquire the speech reception threshold (SRT).Repeatable Battery for the Assessment of Neuropsychological status, adjusted for hearing-impaired individuals (RBANS-H)

Cognitive functioning will be evaluated by use of the RBANS-H [42]. The RBANS assesses five cognitive domains, i.e. Immediate Memory, Visuospatial / constructional, Language, Attention, and Delayed Memory, and consists of 12 subtests.

The domain Immediate Memory consists of two subtests. In the subtest List Learning, the same list of 10 words is presented over four trials, whereas the subtest Story Memory consists of a 12-item short story that is presented twice. After each presentation, the individual must recall as much of the words or the story as possible. Two subtests belong to the domain Visuospatial / constructional: a Figure Copy test, in which the individual is asked to copy a geometric figure, and the subtest Line Orientation, during which the individual needs to match two lines according to their orientation. The domain Language includes the subtests Picture Naming and Semantic Fluency. In the first subtest, 10 line drawings are to be named by the individual. In the second subtest, the individual is given 1 min to generate as many examples as possible from a certain semantic category. The subtests Digit Span and Coding contribute to the domain Attention. In the first subtest, a string of digits is presented, after which the individual is asked to repeat the digits in the correct order. In the subtest Coding, the individual is asked to complete a page of symbols with the corresponding digits according to a key on top of the page. The last domain, Delayed Memory, enquires how many items the individual recalls from the subtests List Learning, Story Memory, and Figure Copy.

The RBANS-H is developed especially for the purpose of examining the cognitive function of individuals with hearing impairment. To reach this purpose, a number of adjustments to the original RBANS have been made. By means of an accompanying PowerPoint presentation, written explanations are given to support the oral instructions and ascertain that the participant understands the instruction. In addition, all relevant stimuli are not only presented orally but also visually. All adjustments were made in accordance to the RBANS guidelines [43]. The total score before and after therapy will be compared in order to reveal any changes in different aspects of cognition due to HD-tDCS.Cortical auditory evoked potentials (CAEP)

Exploratory research is performed towards CAEP as a potential objective measure of therapy effect. Brain potentials will be elicited using an oddball paradigm during which the patient is instructed to press a button every time a rare stimulus (2 kHz) is presented in between frequent stimuli (1 kHz) through shielded headphones (Audio Technica ATH M30x Refaeds). Rare and frequent stimuli will occur with a probability of 20% and 80%, respectively, and the rise and fall time of the presented stimuli are both 5 ms. Stimuli are delivered by use of the Software Presentation™ (Neurobehavioral Systems, Inc). During this task, EEG is recorded (Micromed™ SD LTM 64 Express) using the interface “Gilat Medical TM Event Related Potentials system.” In total, 31 silver/silver chloride (Ag/AgCl) electrodes are placed according to the 10–20 Standard International Electrode System referenced to a chin electrode, with the ground electrode placed on the right mastoid. Vertical electrooculogram (EOG) is recorded using one electrode located below the right eye. After recording the EEG is sampled at 1024 Hz with 22-bit A/D resolution and band passed in the range of 0.02–450 Hz (Micromed™ SD LTM 64 Express).

All data will be analyzed by one researcher using Gilat Medical™ analysis software (Karkur, Israel). Recordings will be segmented into time epochs of 2 s which are time-locked to the stimuli. Baseline correction for each trial will be performed using the average of the 200 ms before stimuli onset for each channel separately. For each patient, all trials will be averaged according to the condition (target and non-target). An Independent Component Analysis (ICA) algorithm will be used to correct for external artefacts, such as eye blinks.

The analysis software will be used to calculate the area below the curve and the center of gravity of peaks within specific time windows in the average trace for the target condition. The time window for the different components is determined according to visual inspection of the average trace over all electrodes. Furthermore, latency average of the correct response is calculated as the time from stimulus onset to the time of the button press. Finally, a group average for the target and non-target records of the baseline measurement and the follow-up measurement is performed in order to compare the averaged response at baseline with the averaged response at the follow-up at three months.

### Sample size and power

The primary outcome is the change in TFI from baseline to follow-up at three months. A TFI decrease of 13 points is considered a minimal clinically important difference. Assuming a standard deviation (SD) of 20 points (SD found in international literature [44] as well as in a previous study of our research group [45]) and a significance level of 0.05, an achieved sample size of 39 per group is required to detect an effect of 13 points with 80% power using a two-sample t-test. Taking into account a possible 20% drop-out, 50 patients will be recruited into each group. Hence, a total of 100 patients will be recruited for the study.

### Assignment of interventions

#### Allocation

Participants will be randomized into the treatment group or the placebo group in a 1:1 ratio. The randomized list will be generated by an independent researcher using QMinim Online Minimization®. The allocation sequence will depend on the date on which participants are referred to the trial. Stratified randomization according to the grade of tinnitus severity on the TFI and gender will be performed. The TFI categorizes patients from grade 1 (slight tinnitus distress) to grade 5 (severe tinnitus distress). As patients with grade 1 are generally not in need of intervention, they will be excluded from the study (inclusion criterion: TFI > 24). Therefore, a total of eight strata will be defined by TFI grade and gender. Patient enrollment and allocation will be performed by an independent researcher.

In order to avoid any test bias, the researcher performing the baseline and follow-up measurements is blinded to the allocation of the patient. The investigator will be unblinded by an independent researcher after the three-month time point (T_1_). The independent researcher will be able to access the randomization sequence via QMinim, an online portal. For technical reasons, it is not possible to blind the investigator administering the HD-tDCS. Therefore, for each patient, the investigator administering the HD-tDCS will differ from the researcher performing the baseline and follow-up measurements.

#### Blinding

Both the patient and the investigator performing baseline and three-month follow-up measurements will be blinded up until and including the three-month time point (T_1_). Patients will be unblinded by an independent clinician at a separate hospital visit following the three-month follow-up time point.

### Data collection, management, and analysis

#### Data collection and management

OpenClinica LLC is used to enter and store data in a clean, secure, and efficient manner. This software package is developed especially for electronic data management in clinical research. Only the principal investigators have access to this password-protected database. Validation checks such as range checks for data values are programmed so that the number of mistakes is minimized. The information collected in this study is kept strictly confidential. Individual information and results are coded, with only the researcher knowing which code was assigned to each participant. The data are kept for 20 years.

#### Statistical methods

Data will be analyzed using SPSS statistical software version 25 (SPSS Inc., Chicago, IL, USA). The primary outcome is the change in TFI from baseline to three months after the treatment. A linear regression model using delta TFI (pre minus post therapy) as an outcome and treatment as a predictor with correction for age, gender, hearing loss, HADS score, and TFI grade will be used as primary outcome analysis. All patients will be used in an intention-to-treat (ITT) analysis.

Per-protocol analyses will be performed for all secondary outcome measurements to evaluate the treatment effect for the compliers. The change in secondary outcomes (which are all continuous variables) from baseline to follow-up at three months will be analyzed with a linear regression model with treatment as predictor controlling for age, gender, hearing loss, HADS score, and TFI grade. The questionnaires that are administered repeatedly over time will be modelled by a linear mixed model using patient as a random intercept to correct for repeated measures coming from the same patient. The Holm-Bonferroni method will be used to correct for multiple testing.

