**Fig. 2 Fig2:**
[figure not shown]
Schedule of enrolment, interventions, and assessments in accordance with the SPIRIT 2013 guidelines. tDCS transcranial direct current stimulation, TFI Tinnitus Functional Index, RBANS-H Repeatable Battery for the Assessment of Neuropsychological status adjusted for hearing-impaired individuals, CAEP cortical auditory evoked potentials

When patients are enrolled in the study, six sessions of sequential dual-site HD-tDCS (or sham stimulation for the control group) are planned within three weeks’ time (twice per week, with at least one day between sessions: T_a_ - T_f_). Stimulation (or sham) is provided for 30 min each session. The electrodes are positioned at the rDLPFC and the LTA. The positioning is according to the 10/20 international system for EEG electrode placement. For the rDLPFC stimulation, the central anode will be placed at F4 and the adjoining cathodes at F2, F6, FC4, and AF4 [24]. For the LTA stimulation, the central anode is positioned at CP5 with adjoining cathodes at C5, TP7, CP3, and P5. A constant current of 2 mA is applied for 15 min at each site with a fade-in and fade-out of 20s, resulting in a total stimulation duration of 30 min. For the sham stimulation, constant current will only be applied for 20s as previously described [30]. The direct current is transmitted by means of five sintered silver/silver chloride (Ag/AgCl) ring electrodes with inner radius of 6 mm and outer radius of 12 mm and delivered by a battery-driven Soterix Medical 1 × 1 tDCS low-intensity stimulator and 4 × 1 multichannel stimulation adaptor (Soterix Medical Inc., New York, NY, USA) with a maximum output of 2 mA. The ring electrodes are stabilized using HD-Electrode holders hooked in the Soterix Medical HD-cap and filled with EEG electrode gel (Neurax, Bonheiden, Belgium) following the guidelines for 4 × 1 HD tDCS stimulation [22].

Immediately after the last HD-tDCS session (T_f_), the patient is instructed to fill in all questionnaires. A follow-up (T_1_) at three months after the baseline measurements will contain the full clinical study protocol: pure tone audiometry, tinnitus analysis, SPIQ/SPIN, questionnaires, RBANS-H, and CAEP. A second follow-up (T_2_) is planned at six months after baseline measurements, comprising only the complete set of questionnaires.

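### The primary regression can use only patients with a three-month TFI, which fits the all-patient ITT statement only if missing values are imputed, and it has no place for the end-of-treatment TFI

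*Protocol article*

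**What the plan says.** The Primary outcome measure section fixes the endpoint: "The primary outcome is the change in the Tinnitus Functional Index (TFI) questionnaire from baseline to follow-up at three months". The Statistical methods section fixes the model: "A linear regression model using delta TFI (pre minus post therapy) as an outcome and treatment as a predictor", adjusted for age, gender, hearing loss, HADS score and TFI grade. It then adds: "All patients will be used in an intention-to-treat (ITT) analysis".

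The Sample size and power section states that "an achieved sample size of 39 per group is required to detect an effect of 13 points with 80% power", and continues: "Taking into account a possible 20% drop-out, 50 patients will be recruited into each group".

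Under Interventions, directly after the last stimulation session (Tf), "the patient is instructed to fill in all questionnaires". A post-treatment TFI is therefore planned for everyone who reaches the end of the sessions.

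The second paragraph of Statistical methods plans a linear mixed model with a random patient intercept for questionnaires given repeatedly. That paragraph deals with secondary outcomes and opens with per-protocol analyses. The document gives no rule for a missing T1 TFI.

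**The concern.** The primary model needs one complete pair of scores (T0 and T1) per patient. Ordinary regression software leaves out anyone who lacks the second score. Read literally, the ITT sentence promises more patients than the model can hold, and the sample size section budgets for just such losses.

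The end-of-treatment TFI is the natural predictor of a missing T1 value, and the trial already collects it. If patients leave between Tf and T1 for reasons related to how they had responded by Tf, and this differs by arm, the regression on those who remain is biased while the data that would correct it sit unused. In a superiority trial, an upward shift under no effect raises the false-positive risk on the primary endpoint.

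**Working it through.** **Inputs from the document.** Difference 13 points ("A TFI decrease of 13 points is considered a minimal clinically important difference"); SD 20 ("Assuming a standard deviation (SD) of 20 points"); significance level 0.05; power 80%; two-sample t-test; 1:1 allocation; drop-out of up to 20%; 100 patients in total. The document gives neither the correlations between visits nor a drop-out mechanism, so these are assumed below.

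**1. The plan's own figure.** Normal approximation: n = 2 × (1.960 + 0.842)² × 20² / 13² = 37.2, so 38 per group. The t-test (noncentral t, two-sided) gives 38.14, so 39 per group with 80.9% power. A one-sided test would need 30, so the stated figure is two-sided. Inflation: 39 / 0.8 = 48.75, so 49, which the plan rounds up to 50. The figures reproduce.

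**2. Who enters the primary model.** At 20% loss, 50 × 0.8 = 40 per group, or 80 of 100. Up to about 20 randomised patients have no change score. Power with 40 per group is 81.9%. With all 50 per group it would be 89.6%, the ceiling if no T1 value were lost.

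**3. How far loss can move the estimate.** The effect in all randomised patients is 0.8 × (effect in completers) + 0.2 × (effect in drop-outs).
- If drop-outs in one arm only differ from that arm's completers by 10 points in mean change, the completer estimate shifts by 0.2 × 10 = 2 points.
- If completers differ between arms by 13 and drop-outs by 0, the effect in all randomised patients is 0.8 × 13 = 10.4.

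**4. Simulated loss driven by Tf response.** Assumptions: 50 per arm, SD 20, correlations T0–Tf 0.65, T0–T1 0.5 and Tf–T1 0.75, about 16–20% lost after Tf. The ranges cover different drop-out rules.

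| Loss depends on Tf response | True effect | Error of completer regression |
|---|---|---|
| In the active arm only | 0 or 13 | about +1.2 to +2.5 |
| Same rule in both arms | 0 | about 0 |
| Same rule in both arms | 13 | about −0.7 to −1.2 |

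An estimate that uses Tf stays within about 0.1 point of the truth in these cases. Its variance changes by about −10% to +2%.

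The third row is not zero because a common rule on the level of response removes different fractions of the two arms once there is a real effect. If the rule works relative to each arm's own mean, the bias is nil at 13 points too.

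As a stress case, let loss run in opposite directions in the two arms, with correlations between the Tf and T1 changes of 0.3, 0.5 and 0.7. Under no effect the completer estimate then averages about 2.0, 3.3 and 4.5 points, while the estimate using Tf averages about 0.

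**5. Size against the noise.** The unadjusted standard error with 40 per group is 20 × √(2/40) = 4.47. A bias of 1.6 is 1.6 / 4.47 = 0.36 standard errors, and moves a two-sided 5% test to about 6.5%. A bias of 2.5 is 0.56 standard errors, and moves it to about 9%.

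**The case against.** **The two statements can coexist.** Regression on the change score and inclusion of all patients are compatible once missing T1 values are imputed, and imputation rules often sit in a full protocol or SAP that is not shown. This stands. A reader might infer that the plan has fixed a completer analysis and that its ITT label is untrue; the document does not establish that. It supports only the narrower statement that the model as written cannot deliver what the sentence says without a step it does not mention.

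**ITT may mean analysed as randomised regardless of compliance.** The section does contrast it with per-protocol analyses, and a patient who stops stimulation can still return for T1. This is a fair reading of the term, but the sentence says all patients.

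**Sizing for drop-out is routine and does not define the analysis set.** Correct. The 20% is also called possible, so it is an allowance and not a forecast.

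**The plan does not ignore Tf altogether.** The mixed model for repeated questionnaires could cover the TFI and use Tf. But it is not the primary analysis, and its population is unclear because its paragraph opens with per-protocol analyses.

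**The mechanism is speculative.** Patients are blinded through T1, and sham patients are offered active treatment afterwards, which gives them a reason to stay. The bar on other tinnitus treatment until three months could work the other way. The document settles neither.

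**Tf helps only those who reach it.** Patients lost during the sessions have no Tf score, and the document does not split the 20%.

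**Conclusion.** The point holds in limited form. As written, the primary model takes only patients with a T1 TFI. With the possible 20% loss, up to about 20 of 100 randomised patients fall outside it, and this does not match the ITT statement unless T1 is imputed. The primary model also leaves out a post-treatment TFI that the trial collects.

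Sample size and power are not affected. The exposure is bias from loss related to Tf response: about 1 to 2.5 points on a 13-point target, in either direction depending on the mechanism, and none under no effect if loss follows the same rule in both arms. These sizes rest wholly on assumed correlations and mechanisms; the larger stress-case values need loss to run in opposite directions in the two arms. The precision gain is modest at best, roughly 0–10% of variance. Using Tf does not correct for loss that depends on unobserved T1 values.

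A reader might take this as a fatal flaw in the primary analysis. The documents do not support that: the bias is conditional, an unseen SAP could supply imputation, and the remedy is cheap. It is a should-fix point.

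**What to change.** Choose one of two routes and state it before unblinding.

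1. Make the primary analysis a likelihood-based repeated-measures model of TFI at Tf and T1, with arm, visit, arm-by-visit, baseline TFI and the listed covariates, and unstructured covariance. Analyse patients as randomised and take the T1 arm contrast as the primary result. Patients with neither Tf nor T1 add nothing to this model, so the analysis set should be described as those with at least one post-baseline TFI.
2. Keep the stated regression and impute missing T1 scores by multiple imputation using T0, Tf and arm. This also brings in patients lost before Tf, and so comes closest to the present ITT sentence.

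Under either route, report the completer regression as a sensitivity analysis, and word the ITT statement to match the set actually analysed. A sensitivity analysis for loss that depends on unobserved T1 values would be a sensible addition. State also whether the mixed model in the secondary paragraph covers the TFI, and in which population.

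Cost: revised analysis wording and slightly more programming, which SPSS 25 can handle. There are no new data, no new visits and no change in sample size.

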Neuronal network activity can be modified by neuromodulation techniques such as transcranial direct current stimulation (tDCS). tDCS is a non-invasive and safe experimental therapy whereby the brain is stimulated with externally applied direct current electric fields in order to modify corticospinal excitability [19]. Effects of tDCS transcend the level of individual neurons, as the technique can influence brain-wide functional connectivity, network synchronization, and oscillatory activity [20]. Recently, the development of high-definition tDCS (HD-tDCS) has enabled researchers to stimulate brain regions with increased focality by using a higher number of smaller electrodes [21, 22]. Clinical applications of tDCS and HD-tDCS include pain relief, especially in fibromyalgia, the treatment of major depressive disorder, and tinnitus [23].

In tinnitus treatment, tDCS and HD-tDCS are mainly applied to two target regions: the left temporal area (LTA) and the right dorsolateral prefrontal cortex (rDLPFC) [24]. The LTA comprises the left auditory cortex, which shows hyperactivation in tinnitus patients [25]. The rDLPFC is involved in the integration of sensory and emotional aspects of tinnitus and is an essential part of the tinnitus distress network [26]. Overall, beneficial effects of tDCS of the rDLPFC have been reported and there are some indications of the benefit of tDCS of the LTA, but randomized controlled trials (RCT) on the effects of tDCS on tinnitus are severely lacking (for review, see [27]). In two recent studies reporting the efficacy of (HD-)tDCS of LTA and rDLPFC in tinnitus treatment, no difference in efficacy was found between the two target regions [24, 28]. Current evidence is too weak to make conclusive recommendations on the use of (HD-)tDCS in tinnitus treatment [23]. As such, there is a need for adequately powered double-blind randomized sham-controlled trials.

This study proposes a RCT with parallel group design, in which participants are randomly allocated to the experimental group or the sham group in a 1:1 ratio. This trial intends to investigate the superiority of HD-tDCS treatment over sham stimulation. It is hypothesized that tinnitus patients receiving six consecutive sessions of sequential dual-site HD-tDCS will report a positive effect on the impact of tinnitus on daily life, as compared to tinnitus patients receiving sham stimulation.

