Except for mild itching or tingling sensations, headaches, or fatigue, no adverse effects of HD-tDCS treatment are expected. In case patients do report serious side effects, HD-tDCS treatment will be discontinued.

No concomitant tinnitus treatment will be allowed between baseline measurement and the three-month follow up. After the three-month time point, participants will be allowed to undergo additional treatment. If participants were allocated to the sham group, they will have the right to undergo an actual HD-tDCS treatment free of cost after the three-month time point.

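### On the likelier reading, all secondary outcomes are analysed only per protocol, with a model that does not in general estimate the complier effect it is meant to estimate

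*Protocol article*

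**What the plan says.** All the relevant text on analysis sets is in the Statistical methods section of the protocol article, in two paragraphs.

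- The first paragraph describes the primary analysis, a linear regression of change in TFI. It closes with "All patients will be used in an intention-to-treat (ITT) analysis".
- The second paragraph turns to the secondary outcomes and opens with "Per-protocol analyses will be performed for all secondary outcome measurements to evaluate the treatment effect for the compliers". The change in each secondary outcome to three months "will be analyzed with a linear regression model with treatment as predictor controlling for age, gender, hearing loss, HADS score, and TFI grade". Questionnaires given repeatedly get a linear mixed model with a random intercept per patient. Holm-Bonferroni is named for multiplicity.

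The Background section sets the aim: "This trial intends to investigate the superiority of HD-tDCS treatment over sham stimulation". The Interventions section gives two rules that could separate adherers from non-adherers after randomisation: "In case patients do report serious side effects, HD-tDCS treatment will be discontinued", and "No concomitant tinnitus treatment will be allowed between baseline measurement and the three-month follow up".

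**The concern.** Randomisation makes the two arms comparable as whole groups. A set restricted to adherers is formed afterwards, by events that treatment or the patient's course may influence. Active patients receive current for 15 minutes at each of two sites and sham patients for only 20 seconds, so tolerance may differ by arm. A patient who takes up a barred treatment before three months may do so because of how the tinnitus is going. Active-arm adherers and sham-arm adherers may then be different kinds of patient, and the difference between them mixes treatment with selection.

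The stated purpose adds a second problem. An effect in compliers refers to one type of patient compared under both treatments. Regressing outcome on arm among those who happened to adhere estimates that only under conditions the plan does not state.

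At stake is the reading of every secondary outcome in a superiority trial, including the TQ, HADS, hyperacusis, speech and cognitive results. They would also rest on a different patient set from the primary TFI result. Holm-Bonferroni adjusts for the number of tests; it does not remove bias from any one of them.

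**Working it through.** **1. The plan's own figure.** The Sample size and power section uses a difference of 13 points, an SD of 20, alpha 0.05 (two-sided assumed) and 80% power. The standardised effect is 13/20 = 0.65. The exact two-sample t-test needs 38.14, so 39 per group, as stated (power 80.9% at 39). With 20% drop-out, 39/0.80 = 48.75, so 49; the plan recruits 50. The figure reproduces. It concerns the primary outcome only, and the choice of set for the secondary outcomes does not change it.

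**2. What the per-protocol model estimates.** Let A be adherence, Z the arm and Y the outcome. The model estimates E(Y | Z=1, A=1) − E(Y | Z=0, A=1), adjusted for the covariates. This is an effect in compliers if the same patients would adhere under either arm, or if adherence is unrelated to outcome given age, gender, hearing loss, HADS score and TFI grade. The plan states neither condition and names no method, such as an instrumental-variable or principal-stratum analysis, that targets a complier effect.

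**3. Size of the shift when exclusion in one arm is related to outcome.** Suppose a fraction q of that arm is excluded and the tendency to be excluded has correlation ρ with a normal outcome. The mean of those kept moves by

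shift in SD = ρ × φ(z_q) / (1 − q).

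With ρ = 1 this is 0.195 for q = 0.10 and 0.350 for q = 0.20. Scaling by ρ:

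| q | ρ = 0.3 | ρ = 0.5 |
|---|---|---|
| 0.10 | 0.3 × 0.195 = 0.06 | 0.5 × 0.195 = 0.10 |
| 0.20 | 0.3 × 0.350 = 0.10 | 0.5 × 0.350 = 0.17 |

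Against the 0.65 SD for which the trial is powered on the TFI, the ends of this range are 0.06/0.65 = 9% and 0.17/0.65 = 26%. The article gives no design effect for any secondary outcome, so this is only a yardstick.

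**4. Effect on type I error.** Simulation with 50 per arm, SD 20, no true effect, 20% excluded in each arm, an unadjusted t-test at 0.05 and 20,000 repetitions:

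| Exclusion and outcome | Bias (points) | Per-protocol error | All-randomised error |
|---|---|---|---|
| Unrelated | 0.0 | 4.9% | 4.9% |
| ρ = 0.3 in both arms | 0.0 | 4.9% | 5.0% |
| ρ = 0.3 in one arm, 0 in the other | 2.1 | 7.2% | 5.0% |
| ρ = 0.5 in one arm, 0 in the other | 3.5 | 12.5% | 4.8% |
| ρ = 0.3 and −0.3 | 4.2 | 15.7% | 4.9% |
| ρ = 0.5 and −0.5 | 7.0 | 36.8% | 4.7% |

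The one-arm rows agree with step 3: 0.105 × 20 = 2.1 and 0.175 × 20 = 3.5 points. The values of q and ρ are assumptions, and the SD of 20 is the TFI figure, used here only as a scale.

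**The case against.** **The intention-to-treat sentence may cover everything.** It is not limited to the TFI, and the next paragraph does not say that per protocol replaces it. Per protocol as an addition is therefore a possible reading. It is the less likely one: the sentence closes the primary paragraph, and per protocol is then assigned to all secondary outcomes with a purpose of its own. If intention-to-treat was meant throughout, the text still has to say so.

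**The bias may be negligible.** Patients are blinded up to and including three months, the course is six sessions in three weeks, and only mild side effects are expected. Adherence may be high and similar in the two arms, and the five covariates may absorb some selection. This stands as a reason why the bias could be near zero. It does not show that it is, since the investigator giving the stimulation is not blinded and the article gives no non-compliance rate. The 20% in the sample size section is drop-out, not protocol deviation.

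**Stronger readings that the documents do not support.** A reader might infer that per protocol favours HD-tDCS. The direction is not established: if sham patients who do poorly more often turn to other treatment, excluding them would work against HD-tDCS. A reader might also count lack of benefit among the reasons for stopping, but the only one the article gives is serious side effects. Nor is the randomised comparison abandoned, because patients are still compared by assigned arm within a subset. If few are excluded, the primary and secondary sets nearly coincide and the secondary results can still inform the primary one. The 36.8% error needs selection of opposite sign in the two arms and is not an expected value.

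**Conclusion.** The point holds in a limited form. As written, and on the likelier reading, the secondary outcomes get only a per-protocol comparison, whose model does not in general estimate the effect claimed for it. The possible bias runs from about zero to about 0.17 SD across the scenarios in which exclusion is unrelated to outcome, related equally in both arms, or related in one arm only. Which of these applies cannot be told from the document, and neither can the sign. The range rests on assumed exclusion rates of 10% to 20%, assumed correlations of 0.3 to 0.5, a normal outcome and no covariate adjustment.

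This should be fixed, but it does not threaten the main conclusion of the trial: the primary TFI analysis has its intention-to-treat set. The absence of a definition of the per-protocol set is not counted here, since it may be in a document not shown.

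**What to change.** In Statistical methods, replace the opening sentence of the secondary-outcome paragraph with one stating that all secondary outcomes are analysed first in all randomised patients by assigned arm, using the models already named. Keep per protocol as a supportive analysis, labelled as such. Delete the reference to the effect in compliers, or name a method that targets that effect and state its assumptions.

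The cost is one sentence and a second run of the same models; no additional patients or measurements are needed. The change should be made before unblinding, because a choice of analysis set made once results are known is hard to defend. A per-protocol run of the primary TFI may be added, but that is a preference and corrects no error.
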